#### Health Economics Endpoints

- Total cost of treatment and resource utilization from Baseline through end of study (RUI)
- Change in economic value from Baseline to 26 weeks, 52 weeks, 2 years and 3 years post first lead placement.

## 8. Design

The Vercise DBS Registry for Dystonia is a prospective, on-label, multi-center, international registry.

### 8.1. Scale and Duration

The study will be conducted at up to 40 international centers. Up to 200 subjects will be implanted. Follow-up of each subject will continue for three years after first lead placement. The study may require up to five calendar years to complete.

**Figure 8.1-1: Vercise DBS Dystonia Registry Study Design**

[figure not shown]

## **8.2. *Treatment Assignment***

Subjects who provide written informed consent will be considered enrolled in the study and therefore assigned a unique subject identifier in the Electronic Data Capture (EDC) system.

Consented subjects who successfully pass all screening requirements will receive the Vercise™ System.

## **8.3. *Justification for the Study Design***

All devices used in this registry are approved for commercial use.

The endpoints of this registry are intended to provide a broad evidence base to assess long-term clinical and economic outcomes of the Vercise System in a large number of subjects representing ‘real-world’ use patterns. The registry will also bridge the existing evidence gap in disease management, treatment effectiveness, health economic value, and patient outcomes for on-label use of the system.

# **9. Subject Selection**

## **9.1. *Study Population and Eligibility***

Up to 200 implanted subjects may be included in the registry.

Subjects will generally be recruited from physician’s practice and will be eligible to receive Deep Brain Stimulation to treat their Dystonia using the commercially-approved BSC Vercise System per local DFU.

## **9.2. *Inclusion Criteria***

Subjects who meet all of the following criteria (see Table 9-1) may be given consideration for inclusion in this clinical investigation, provided no exclusion criterion (see Section 9.3) is met.

**Table 9-1: Inclusion Criteria**

|                           |                                                                                                                                                                                                                                                                                                                                                                                                                                                                                                                                                                                                                                |
|---------------------------|--------------------------------------------------------------------------------------------------------------------------------------------------------------------------------------------------------------------------------------------------------------------------------------------------------------------------------------------------------------------------------------------------------------------------------------------------------------------------------------------------------------------------------------------------------------------------------------------------------------------------------|
| Inclusion Criteria | 
IC1. Understands the study requirements and the treatment procedures and provides written informed consent before any study-specific tests or procedures are performed.
 
IC2. Receive currently available Vercise System and any new CE marked components (i.e., leads, extension, Pocket Adaptor, CP, etc.) compatible with the Vercise System
 
IC3. Meets criteria established in the locally applicable Vercise System Directions for Use (DFU) for Dystonia.
 
IC4. At least 7 years old. Parent or guardian consent is required in patients who are younger than 18 years at the time of consent.
 |
|---------------------------|--------------------------------------------------------------------------------------------------------------------------------------------------------------------------------------------------------------------------------------------------------------------------------------------------------------------------------------------------------------------------------------------------------------------------------------------------------------------------------------------------------------------------------------------------------------------------------------------------------------------------------|

### **9.3. Exclusion Criteria**

Subjects who meet the following criterion (Table 9-2) will be excluded from this clinical study.

**Table 9-2: Exclusion Criteria**

|                           |                                                                                                     |
|---------------------------|-----------------------------------------------------------------------------------------------------|
| Exclusion Criteria | 
EC1. Meets any contraindication in the Vercise System locally applicable Directions for Use.
 |
|---------------------------|-----------------------------------------------------------------------------------------------------|

## **10. Subject Accountability**

### **10.1. Point of Enrollment**

A patient will be considered enrolled in this study after he/she signs and dates the informed consent form (ICF). No study-related procedures or assessments can take place until the informed consent form is signed.

### **10.2. Withdrawal**

All subjects enrolled in the clinical study (including those withdrawn from the clinical study or lost to follow-up) shall be accounted for and documented. If a subject withdraws from the clinical investigation, the reason(s) shall be reported. If such withdrawal is due to problems

related to investigational device safety or performance, the investigator shall use local treatment protocols to determine the subject's options for therapy.

Reasons for withdrawal could include but are not limited to

- physician discretion,
- subject choice to withdraw consent; in case of subjects under the age of 18 years old, parent/guardian choice to withdraw consent will be considered a valid reason for withdrawal.
- subject's failure to meet registry inclusion or exclusion criteria after enrollment but prior to system implant,
- failure to receive a BSC DBS system,
- lost to follow-up, or
- death.

While study withdrawal is discouraged, subjects may withdraw from the study at any time, with or without reason, and without prejudice to further treatment.

All applicable case report forms (CRFs) up to the point of subject withdrawal and an "End of Study" form must be completed. Any subject deemed "lost to follow-up" should have a minimum of three documented attempts to contact him/her prior to completion of the "End of Study" form.

Additional data may no longer be collected after the point at which a subject has been withdrawn from the study or withdraws consent, for whatever reason. All open adverse events should be closed or documented as unresolved. Data collected up to the point of subject withdrawal may be used and analyzed.

Subjects withdrawn after completing the implant procedure will not be replaced and will be included in the site's overall total for implanted subjects.

### ***10.3. Subject Status and Classification***

A subject is considered enrolled after a signed informed consent form (ICF) has been obtained. Study participation will end when an implanted subjects completes their 3 Year follow up visit.

### ***10.4. Enrollment Controls***

Enrollment will remain open until one of the following events occurs:

- 200 subjects are implanted.

- The study is terminated at any time, at the Sponsor's discretion.

Enrollment controls will be implemented per the Enrollment Communication Plan developed for this study.

## **11. Study Methods**

### **11.1. *Data Collection***

The data collection schedule is shown in Table 11-1. Assessments and questionnaires should be utilized based on subject classification and age, and as highlighted in Table 11-2.

Specific questionnaires or parts of questionnaires may not be applicable due to age or type of dystonia.

**Table 11-1: Data Collection Schedule**

| Data collection variable/ Study assessment*                 | Screening | Pocket Adaptor (PA)
with MDT IPG ON | Baseline visit
(Up to 90 days post ICF) | Implant procedures
Day 0
(Leads, IPG) | Activation | Week 12 Visit
(84 days ± 21) | Week 26 Visit
(182 days ± 21) | Week 52 Visit
(365 days ± 56) | Year 2 Visit
(730 days ± 56) | Year 3 Visit
(1095 days ± 56) | Unscheduled visits
(anytime) |
|-------------------------------------------------------------|-----------|----------------------------------------|--------------------------------------------|---------------------------------------------|------------|---------------------------------|----------------------------------|----------------------------------|---------------------------------|----------------------------------|---------------------------------|
| Adverse Event (AE) †                                        |           | X                                      | X                                          | X                                           | X          | X                               | X                                | X                                | X                               | X                                | X                               |
| Burke-Fahn-Marsden Dystonia Rating Scale (BFMDRS)           |           | X                                      | X                                          |                                             |            |                                 | X                                | X                                | X                               | X                                |                                 |
| Clinical Global Impression of Change (CGI-C)‡               |           | X                                      |                                            |                                             |            |                                 | X                                | X                                | X                               | X                                |                                 |
| Clinical Global Impression of Change (CGI-C: Sub)‡          |           | X                                      |                                            |                                             |            |                                 | X                                | X                                | X                               | X                                |                                 |
| Clinical Global Impression of Change (CGI-C: Crg)‡          |           | O                                      |                                            |                                             |            |                                 | O                                | O                                | O                               | O                                |                                 |
| Concomitant Medications                                     |           |                                        | X                                          |                                             | X          |                                 | X                                | X                                | X                               | X                                |                                 |
| Demographics                                                |           |                                        | X                                          |                                             |            |                                 |                                  |                                  |                                 |                                  |                                 |
| Global Dystonia Rating Scale (GDS)                          |           | X                                      | X                                          |                                             |            |                                 | X                                | X                                | X                               | X                                |                                 |
| Genetic testing results                                     | O         |                                        |                                            |                                             |            |                                 |                                  |                                  |                                 |                                  |                                 |
| Inclusion/exclusion criteria evaluation                     | X         |                                        |                                            |                                             |            |                                 |                                  |                                  |                                 |                                  |                                 |
| Informed consent form§                                      | X         |                                        |                                            |                                             |            |                                 |                                  |                                  |                                 |                                  |                                 |
| Medical history                                             |           |                                        | X                                          |                                             |            |                                 |                                  |                                  |                                 |                                  |                                 |
| Monopolar review                                            |           |                                        |                                            |                                             | O          |                                 |                                  |                                  |                                 |                                  |                                 |
| Montreal Cognitive Assessment (MoCA)                        |           | X                                      | X                                          |                                             |            |                                 | X                                | X                                | X                               | X                                |                                 |
| Procedural information                                      |           |                                        |                                            | X                                           |            |                                 |                                  |                                  |                                 |                                  |                                 |
| Programming parameters                                      |           | X                                      |                                            |                                             | X          |                                 | X                                | X                                | X                               | X                                |                                 |
| Impedance recordings                                        |           | O                                      |                                            |                                             | O          |                                 | O                                | O                                | O                               | O                                |                                 |
| Resource Utilization Inventory (RUI)                        |           | X                                      | X #                             |                                             |            |                                 | X                                | X                                | X                               | X                                |                                 |
| Satisfaction with Treatment (SWT)‡                          |           | X                                      |                                            |                                             |            |                                 | X                                | X                                | X                               | X                                |                                 |
| Short Form Health Survey-10 (SF-10v2)                       |           | X                                      | X #                             |                                             |            |                                 | X                                | X                                | X                               | X                                |                                 |
| Short Form Health Survey-36 (SF-36v2)                       |           | X                                      | X #                             |                                             |            |                                 | X                                | X                                | X                               | X                                |                                 |
| Toronto Western Spasmodic Torticollis Rating Scale (TWSTRS) |           | X                                      | X                                          |                                             |            |                                 | X                                | X                                | X                               | X                                |                                 |

\* Assessments and questionnaires should be utilized based on subject classification and age, and as highlighted in Table 11-2. Baseline Clinician administered assessments done as part of standard of care screening to determine eligibility for DBS up to 180 days prior to baseline may be used for this Baseline Visit (no repetition needed).

Pocket Adaptor (PA): Subjects receiving a pocket adaptor to connect non-BSC leads to BSC IPG

X = required; O = optional

† Only adverse events related to the device, stimulation, or procedure, and serious adverse events will be recorded

‡ In PA patients, data for CGI-C, and SWT at Pocket Adaptor Visit will be collected in comparison with patient condition before receiving non-BSC implant. At follow-up visits, these data will be collected in comparison to patient STIM OFF condition at Baseline.

# For PA patients, not to be completed at Baseline

§ In subjects younger than 18 years of age, form should be completed by both the subject and the parent/guardian.

**Table 11-2: Data Assessment**

| Assessment and Questionnaires                                     | Subject classification by diagnoses and age                     |
|--------------------------------------------------------------------------|------------------------------------------------------------------------|
| Burke-Fahn-Marsden Dystonia Rating Scale (BFMDRS)                        | Subjects with non-cervical dystonia;                                   |
| Clinical Global Impression of Change (Clinician - CGI-C)                 | All subjects                                                           |
| Clinical Global Impression of Change (Subject - CGI-C: Sub)              | All subjects                                                           |
| Clinical Global Impression of Change (Caregiver – CGI-C:Crg)
OPTIONAL | All subjects                                                           |
| Global Dystonia Rating Scale (GDS)                                       | All subjects                                                           |
| Montreal Cognitive Assessment (MoCA)                                     | All subjects                                                           |
| Resource Utilization Inventory (RUI)                                     | All subjects                                                           |
| Short Form Health Survey-36 (SF-36v2)                                    | Subjects aged 18 years and older at time of consent                    |
| Short Form Health Survey-10 (SF-10v2)                                    | Subjects under the age of 18 years at time of consent                  |
| Satisfaction with Treatment (SWT)                                        | All subjects                                                           |
| Toronto Western Spasmodic Torticollis Rating Scale (TWSTRS)              | Subjects with cervical dystonia; 18 years and older at time of consent |

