### 12.1.1. Responder Rate

A responder is defined as a subject with 30% or greater reduction in Baseline BFMDRS or TWSTRS score in non-cervical and cervical dystonia subjects, respectively. The responder rate is calculated as the number of responders divided by the number of subjects within each subgroup. Because the number of responders follows a binomial distribution, the 95% confidence interval for the proportion of responders will be calculated using the Clopper-Pearson method.

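### Table 11-2 assigns neither BFMDRS nor TWSTRS to cervical dystonia subjects under 18, who are eligible and counted in the responder-rate denominator but cannot be classed as responders

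*Protocol*

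**What the plan says.** Four parts of the protocol bear on this.

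- **Eligibility.** Table 9-1 sets the lower age limit: "IC4. At least 7 years old". The only exclusion criterion (Table 9-2) is a contraindication in the local Directions for Use. Neither table excludes cervical dystonia below 18.
- **Scale assignment.** In Table 11-2 the BFMDRS row reads "Subjects with non-cervical dystonia", with no age clause. The TWSTRS row reads "Subjects with cervical dystonia; 18 years and older at time of consent".
- **Which table governs.** Section 11.1 states: "Assessments and questionnaires should be utilized based on subject classification and age, and as highlighted in Table 11-2". The Baseline, Week 26, Week 52/Year 2 and Year 3 sections list both scales but refer to Table 11-2 for which one applies.
- **Endpoint.** Section 12.1.1 defines a responder by a 30% or greater "reduction in Baseline BFMDRS or TWSTRS score in non-cervical and cervical dystonia subjects, respectively". The Statistical Test row of the synopsis makes the same split. On the denominator, Section 12.1.1 says: "The responder rate is calculated as the number of responders divided by the number of subjects within each subgroup". The ITT set in Section 12.2.1 is every enrolled subject who undergoes an implant procedure.

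**The concern.** The two scale rows in Table 11-2 do not cover the eligible population. A cervical subject who is 7 to 17 at consent falls outside both. Because age is fixed at consent, turning 18 during the three years of follow-up does not bring the subject under the TWSTRS row. The responder definition then requires a TWSTRS score that Table 11-2 does not assign.

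The responder rate is the endpoint on which the registry is sized, and Section 12.1.2 treats it as primary. A subject who cannot respond by construction, but who stays in the denominator, pulls the rate down. If such subjects are left out instead, the subgroup shrinks and the interval widens. The analysis plan can settle which of the two happens, but it cannot supply a pre-implant rating that was never made.

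**Working it through.** **1. Cross age with classification.** Inputs are Table 9-1 (IC4), Table 11-2 and Section 12.1.1.

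| Classification | Age at consent | Scale in Table 11-2 | Scale needed by 12.1.1 | Responder status possible? |
|---|---|---|---|---|
| Non-cervical | 7–17 | BFMDRS | BFMDRS | Yes |
| Non-cervical | 18+ | BFMDRS | BFMDRS | Yes |
| Cervical | 18+ | TWSTRS | TWSTRS | Yes |
| Cervical | 7–17 | none | TWSTRS | No |

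One of the four cells is empty.

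**2. What these children do have.** Table 11-2 gives GDS, CGI-C and CGI-C: Sub to all subjects, and SF-10v2 to those under 18. Section 14.7 describes GDS as a severity scale with a maximum of 140. Section 7 makes change in GDS a clinical endpoint at all four follow-ups. The loss is confined to the responder outcome and the BFMDRS/TWSTRS change scores.

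**3. The plan's own sample size.** Inputs from Table 12.1: total N = 200, subgroup prevalence 0.25, attrition 30%, assumed rate 0.15, target 95% CI width 0.30, probability 0.95. The interval is Clopper-Pearson (Section 12.1.1).

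- Secondary subgroup implanted: 200 × 0.25 = 50.
- Evaluable after attrition: 50 × 0.70 = 35.
- Exact binomial probability at 0.15 that the Clopper-Pearson width is at most 0.30 with n = 35: 0.931, against the stated 0.95. The smallest n reaching 0.95 is 37.

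The stated design is thus close to reproduced, and this point does not depend on that small difference.

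**4. Effect per child if counted in the denominator as worded.** Take full enrolment and 50 implanted in the secondary subgroup.

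- Ceiling, if the child would have responded: 1/50 = 0.020, or 2 percentage points.
- Expected, if the child responds with the assumed probability: 0.15 × 1/50 = 0.003, or 0.3 points.
- Primary subgroup, 200 − 50 = 150 implanted: ceiling 1/150 = 0.0067, or about 0.7 points. Table 12.1 gives no assumed rate for this subgroup, so no expected value is given.

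**5. Illustration by share affected.** The protocol gives no share, so 5%, 10% and 20% are assumptions. They are applied to the 35 evaluable subjects in the secondary subgroup, with n rounded.

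| Assumed share unscored | Rate read if kept in denominator, true rate 0.15: 0.15 × (1 − share) | n if excluded | Probability of CI width ≤ 0.30 |
|---|---|---|---|
| 0% | 0.150 | 35 | 0.931 |
| 5% | 0.143 | 33 | 0.889 |
| 10% | 0.135 | 32 | 0.805 |
| 20% | 0.120 | 28 | 0.587 |

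**6. Can BFMDRS serve cervical subjects?** Section 14.2 includes the neck among its nine body areas and halves the neck score. With severity and provoking factor each at most 4, the neck contributes at most 4 × 4 × 0.5 = 8 of 120. A 30% relative reduction can still be calculated on that basis, but it rests on a narrow range when only the neck is affected.

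**The case against.** Several counter-arguments have force.

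- **The stratum may be empty.** The protocol does not say how many cervical subjects under 18 are expected. This stands, and it limits the importance of the point.
- **These children are not without efficacy data.** A reader might infer from the empty cell that they have no severity or efficacy score at any visit. The documents do not support that, as step 2 of the working shows.
- **Two points per child is a ceiling.** A reader might take it as the expected loss. It applies only when the child would certainly have responded; at the assumed rate the expected loss is about one seventh of it (0.3/2).
- **Section 12.1.1 gives a general formula and no missing-score rule.** The analysis plan could exclude unscored subjects. That is possible, but the only denominator the protocol states counts everyone in the subgroup, and exclusion would not give these children an outcome.
- **The visit sections call Table 11-2 guidance, and Section 11.1 foresees that some instruments may not apply because of age or type of dystonia.** A site might therefore rate a child anyway. The footnote to Table 11-1 also lets earlier standard-of-care clinician ratings serve as baseline, so some baselines could be recovered. Both are true, but neither assigns a scale to these subjects. The TWSTRS age limit may well be deliberate, since its disability items include work and driving (Section 14.15).
- **The BFMDRS cell ends in a semicolon, so an age clause may have been lost.** This is a fair caution about the table cell. The synopsis and Section 12.1.1 make the same split without such a clause, so the responder definition would still lack a rule for these children.

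**Conclusion.** The gap is real. As written, the protocol admits cervical subjects aged 7 to 17, assigns them neither scale on which response is defined, and keeps them in the responder denominator. They have no responder outcome and no BFMDRS or TWSTRS change score; their other clinical endpoints are unaffected.

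The total effect cannot be given because the number of such children is not stated. The per-child figures rest on full enrolment of 200, a secondary share of 0.25, and the denominator being applied as worded. The expected figure also assumes that these children respond at the overall assumed rate.

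This should be fixed, because it touches the endpoint that sizes the registry and the repair is small. It does not threaten the registry as a whole: the analysis is descriptive and single-arm, and the affected group is probably small.

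**What to change.** Reconcile Table 11-2, IC4 and the responder definition so that every eligible subject has one assigned scale. One way is to extend the BFMDRS row of Table 11-2 to add cervical dystonia under 18 years at time of consent, and to state in Section 12.1.1 and the Statistical Test row of the synopsis that response in these subjects is judged on BFMDRS. If that route is taken, note the halved neck weighting and the resulting narrow score range beside the definition.

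For any such subject already enrolled without a baseline BFMDRS or TWSTRS score, report GDS change. Report the responder rate twice, once with these subjects counted as non-responders (the current wording) and once with them excluded, and give their number in each subgroup. Showing both keeps the ITT set visible and lets the reader see how much the gap matters.

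The cost is one table cell, a sentence in each of two places, a CRF logic change, and one short clinician rating at each assessment visit for what are likely to be few children.
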